## Abstract

**Background:**

The current and declining physical activity levels of children is a global concern. Integrating physical activity into the school curriculum may be an effective way not only to improve children’s physical activity levels but also enhance educational outcomes. Given the recent national focus in Australia on improving the literacy levels of children in primary school, and an increasing proportion of time spent on explicitly teaching these skills, integrating physical activity into English could be a viable strategy to improve literacy levels and physical activity at the same time. The aim of this study is to evaluate the impact of the ‘Thinking While Moving in English’ (TWM-E) program on children’s physical activity, on-task behavior in the classroom, academic achievement, and executive function.

**Methods:**

Grade 3–4 children from 10 public schools in New South Wales, Australia will be randomly allocated to intervention (*n* = 5) or control (*n* = 5) groups. All teachers will receive 1-day workshop of registered professional learning and a TWM-E equipment pack (e.g., chalk, lettered bean bags). Intervention schools will be asked to adapt their English lessons to embed movement-based learning in their daily program for three 40-min lessons per week, over a six-week period. The primary outcome is children’s physical activity levels across the school day (measured using accelerometry). Secondary outcomes are children’s on-task behavior during English lessons, academic achievement in English, and executive function. A detailed process evaluation will be undertaken including questionnaires, fidelity checks, and teacher and student interviews.

**Discussion:**

The TWM-E program has the potential to improve primary school children’s physical activity levels, along with academic outcomes (on-task behavior, cognition, and academic achievement), and provide stakeholders with exemplar lessons and guidelines which illustrate how to teach English to children whilst they are moving.

**Trial registration:**

Australian and New Zealand Clinical trial Register ACTRN12618001009202

Date registered: 15/06/2018 retrospectively registered.

**Electronic supplementary material:**

The online version of this article (10.1186/s12889-019-6635-2) contains supplementary material, which is available to authorized users.

## Background

Participation in physical activity in children is in decline, and this is a concern because physical inactivity is associated with a range of chronic illnesses such as obesity, high blood pressure, type II diabetes, and some cancers [1, 2]. Physical activity can also prevent mental health disorders (e.g., anxiety and depression), and enhance psychological health (e.g., well-being) [3, 4]. Additionally, improvements in physical activity and fitness have been shown to increase students’ school engagement, as well as enhance their cognitive and academic performance [5–8].

Despite the numerous benefits of physical activity, very few children and adolescents are sufficiently active [9]. National and international physical activity recommendations suggest that children should spend at least 60 min in daily physical activity to achieve optimal health outcomes [10–13]. However, reports show that only 19% of Australian children and adolescents meet these recommendations [14, 15].

The International Society for Physical Activity and Health (2012) [16] considers schools as one of the best “investments” for promoting physical activity. School-based programs have been shown to increase children’s physical activity levels [17, 18]. A multi-component approach for encouraging physical activity in schools typically involves the delivery of quality physical education, activity before, during, and after the school day, as well as staff, family, and community involvement [17, 19]. However, the authors of two systematic reviews and meta-analyses concluded that the effects of school-based interventions on objectively measured physical activity are minimal [20, 21]. A possible reason could be that physical activity interventions are rarely implemented as intended, with teachers reporting that lack of time as the most common barrier [18, 22].

A recent systematic review proposed a conceptual model describing neurobiological, psychosocial, and behavioral mechanisms that may account for the positive effects of physical activity on academic outcomes in young people [23]. Neuroimaging studies in children have examined the structural and functional brain changes associated with participation in physical activity. For example, the FitKids trial [24] found that children who participated in a 9-month physical activity program improved their performance on cognitive tasks and demonstrated more mature brain activation patterns in the right anterior prefrontal cortex.

A range of psychosocial mechanisms (e.g., motivation, perceptions of novelty, and attitudes toward physical activity) have emerged as potential mediators of the effects of physical activity on academic outcomes. Although there is little experimental evidence, it is plausible that engagement in physically active lessons may increase students’ enjoyment and interest, and this may indirectly enhance learning. Pesce (2012) [25] suggested that goal-directed, cognitively demanding physical activity can activate the same neurons in the brain that are used to control complex cognitive processes. Finally, on-task behavior is a key predictor of academic success [26] and may explain the effects of school-based physical activity on children’s learning and academic performance.

Growing evidence supports the positive effects of: (i) active recess (i.e., providing opportunities for students to be active during recess and lunch breaks), (ii) classroom physical activity breaks (i.e., short activity breaks delivered in the classroom, known also as energiser breaks), and iii) physically active lessons (i.e., lessons that integrate physical activity into other key learning areas), to increase students’ on-task behavior, academic achievement, and physical activity levels [7, 27]. Among these, the physically active academic lessons have been studied the least.

Physically active academic lessons have the potential to increase children’s physical activity levels during the school day without compromising academic time [19, 27]. Concomitantly, embedding movement-based learning into academic instruction can enhance children’s learning performance [28–35]. Physically active environments have also been shown to improve children’s executive functions [36–38]. Importantly, the core executive functions (i.e., inhibition, shifting, and updating [39]) are fundamental for children’s physical, emotional, psychological, and social development and have been linked with school readiness and academic success [40–42].

A previous iteration of the “Thinking While Moving program” in Maths (TWM published as EASY MINDS) aimed at numeracy, and a pilot version of the “Thinking While Moving in English” (TWM-E) produced promising results when physically active academic lesons are integrated during learning: The TWM in Maths program involved a successful randomized controlled trial (RCT), consisting of 3 × 60 min physically active mathematics lessons for six weeks [34]. Compared with the control group, the intervention group showed higher physical activity during the Mathematics lessons, and on-task behavior. The program was rated as providing positive experiences for teachers and students, both in terms of enjoyment and engagement [35]. A recent TWM-E feasibility trial was carried out in a single school for four weeks and all lesson plans were organized and delivered by the research team [43]. Improvements favoring the intervention group were found in on-task behavior and spelling scores in Grade 4 students. Taking into account effective strategies and teachers’ feedback utilized in the previous “Thinking While Moving” programs the next phase will include a cluster RCT of the TWM-E.

The study described in this protocol will extend the TWM in Maths intervention to English. The TWM-E intervention will involve integrating physical activity into English lessons in primary schools. Current curriculum recommendations in New South Wales (NSW), Australia require primary school students to spend 25–35% of a school week in English lessons, 20% in Mathematics and only 6–10% in Personal Development, Health and Physical Education (PDHPE [44]). Despite this strong emphasis on literacy, national and international assessments indicate that about one quarter of Australian students achieve literacy results at or below the minimum standards [45, 46].

There is clearly a strong rationale for reconsidering the design and delivery of literacy programs in Australian primary schools to reinvigorate English lessons with interactive movement-based learning, given the proportion of time children spend on this traditionally sedentary subject. Combining literacy curricula with physical activity may also have positive effects on both physical and cognitive outcomes (e.g., memory, attention, goal-directed behavior).

### Aims and hypotheses

The overall aim of this RCT is to evaluate the effect of integrating physical activity into English lessons on children’s school-based physical activity, on-task behavior, learning and cognition (i.e., executive function).

The specific research questions for this study include:i)What is the impact of the TWM-E intervention on the primary outcome, physical activity during the school day?ii)What is the impact of the TWM-E intervention on the secondary outcomes, on-task behavior during English lessons, academic achievement in English and executive function?

It is hypothesized that the TWM-E group will show improvements in all measures compared to the control group.

## Methods/design

### Participants

TWM-E will be evaluated using a two-arm pararell group cluster RCT with an intervention and a wait-list control group. Stage 2 teachers (Grade 3 & 4) from 10 government primary schools of the Hunter Region, NSW, Australia will be invited to participate. Stage 2 includes the first year of the Australian National Assessment Program for Literacy and Numeracy (NAPLAN) testing in Grade 3 and thus it has been selected as the ideal time for teachers to consolidate identified literacy skills through increasing on-task behavior and engagement [47, 48]. Baseline data collection will occur in the school term preceding the intervention delivery (i.e., Term 2, May to June 2018). The intervention delivery will be conducted in Term 3 (i.e., July to September 2018). Post-test data collection will commence midway through Term 3 and will contintue until the end of the term.

Ethics Approval has been sought and obtained from the University of Newcastle, Australia (No: H-2017-0240), and the NSW Department of Education (SERAP No: 2017368). The TWM-E trial is registered with the Australian and New Zealand Clinical Trials registry (ACTRN12618001008213). Schools will be randomly selected from a metropolitan area (within a 60 km radius of the University of Newcastle). School principals will receive an initial invitation letter followed by an email. Principals, teachers, and parents will need to provide written consent forms for each child to participate.

The design, conduct, and reporting of the TWM-E program will adhere to the Consolidation Standards of Reporting Trials (CONSORT) guidelines and the extension for cluster RCTs [49]. Participating schools will be stratified and pairs of schools will be matched according to their enrolment size and demographics (e.g., literacy program, socio-economic status and location), using the index of community socio-educational advantage (ICSEA). The ICSEA value includes data and information regarding family background (e.g., parental occupation, school/ non-school education achieved) provided to schools directly by families. Following baseline assessments, an independent researcher not involved in the project will use a random number producing algorithm to randomly assign each pair of matched schools to either control or the treatment condition. This method will ensure the same likelihood of allocation into one of the two study arms for all schools. Figure 1 shows the flow of participants. Schools in the waitlist control arm will continue with usual practice, which may include some schools pursuing other physical activity promotion initiatives. No restrictions will be made regarding schools’ participation in such programs, but they will be asked to provide details of their involvement. However, during recruitment, schools that are currently participating in physical activity programs run by the University (e.g., iPLAY [50]) will not be targeted for inclusion.

**Fig. 1 Fig1:**
[figure not shown]
Flow of participants

### Sample size calculation

Power analysis using procedures appropriate for a cluster RCT study design [51] were conducted to determine the sample size required to detect changes in the primary outcome of accelerometer-determined physical activity counts per minute (CPM). Calculations assumed baseline to post-test correlation scores of *r* = 0.30 and were based on 80% power and alpha level 0.05. Based on the reported physical activity effects (i.e., *SD* change = 200 CPM) after six weeks of the TWM in Maths study pilot study, and a conservative intra-class correlation coefficient (ICC = 0.15), a study sample of *N* = 200 with 8 clusters (i.e., schools) of 25 students would provide adequate power to detect a between group difference of 200 CPM across the school day [34, 52].

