### Intervention

TWM-E will involve teachers adapting 3 × 40 min English lessons per week over a 6-week period. Movement-based learning will be incorporated during teaching selected curriculum from the NSW K-6 English syllabus. The program delivery will involve the following components: (i) full-day professional learning for teachers, (ii) TWM-E equipment pack, (iii) handbook for teachers with examples on how to incorporate movement-based learning into English lessons, (iv) online and PDF resources with lesson examples developed by the research team, (v) three observations with feedback per school by members of the research team during program implementation, which will also function as a fidelity check, and (vi) weekly newsletter emails providing implementation strategy support (i.e., separate advice and tips per school based on observations by the research team).

Firstly, participating teachers will attend a full-day professional learning workshop conducted at the University and delivered by the research team. The professional learning day will be registered and accredited with the National Educational Standards Authority (NESA [53]; NSW Department of Education, 2017). Teachers will earn professional learning hours towards their teacher accreditation (Highly Accomplished Standards 1.2.3, 2.5.3, 4.1.3, 6.3.3). The purpose of this workshop will be to help teachers familiarize themselves with the process of integrating movement-based learning with appropriate English syllabus content. A training model is useful for the dissemination of key knowledge to be used in the intervention. The mentoring model [54, 55] is underpinned by situated learning theory [56] and contextualizes the theoretical content presented to teachers. A summary of the workshop’s content is presented in Table 1.

**Table 1 Tab1:** Summary of the professional learning workshop

1. Course rationale	• Presentation of current research findings that identify prevalence and issues around physical activity, cognitive performance and the K-6 English curriculum
2. Evidence for TWM-E	• Findings of the feasibility trial and comparison with the previous Thinking while Moving in Maths research project

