### Physical activity

The primary outcome will be children’s physical activity levels during the school day. Objective measurements of intensity and physical activity levels (i.e., counts per minute) will be obtained using tri-axial wrist-worn accelerometers AX3 (Axivity, York, UK). AX3 accelerometers have been found to be a valid and reliable tool for measuring movements [60] [61].

Accelerometers will be distributed on Monday morning and will be collected Friday afternoon. They will be worn for five consecutive school days from 9:00 am to 3:00 pm. Teachers will be trained to assist their students with placement of the accelerometers. They will distribute and collect the accelerometers daily which will be coded for individual students. Accelerometer data will be downloaded in raw format using OmiGui Software and processed in R software (http://cran.r-project.org/) using the software package GGIR [62]. Data extracted between Monday – Friday (9 am – 3 pm) will be retained for the analysis. Non-wear time will be classified within a 60-min time window if for at least two out of the three axes [63]. Data will be reduced by calculating the average gravity-based acceleration units (g), per 1-s epoch, with daily time spent in moderate-to-vigorous physical activity (MVPA) determined using the sum of epochs averaging above 142 mg [64]. The average minutes spent in MVPA per day and average daily wear time will be computed using data from each participant’s valid days. A valid day will be defined as > 5 school hours on any given day [34], with participants included in the analysis if they wear the monitor for at least 3 days [65].

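### The 80% power stated for 8 schools relies on a large-sample formula and an ambiguous SD; the 10 schools planned largely restore it at 200 CPM, but that whole-day target is not reconciled with the lesson time

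*Protocol article*

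**What the plan says.** The section Sample size calculation states that the calculations "were based on 80% power and alpha level 0.05". "Calculations assumed baseline to post-test correlation scores of *r* = 0.30". The variability input is given as "Based on the reported physical activity effects (i.e., *SD* change = 200 CPM", attributed to the earlier maths programme, with an ICC of 0.15. The conclusion is that N = 200, as "8 clusters (i.e., schools) of 25 students would provide adequate power to detect a between group difference of 200 CPM across the school day".

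The Abstract and the Participants section plan 10 schools, five per arm, allocated within matched pairs. The article does not connect the 8 schools of the calculation with the 10 of the design.

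On lesson time, the Intervention section says "TWM-E will involve teachers adapting 3 × 40 min English lessons per week over a 6-week period". The Background describes the maths trial as "consisting of 3 × 60 min physically active mathematics lessons for six weeks" and reports its activity gain as occurring during the mathematics lessons. On measurement, the Physical activity section says of the accelerometers: "They will be worn for five consecutive school days from 9:00 am to 3:00 pm".

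**The concern.** Three things in the sample size paragraph do not sit well together.

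- **Few clusters.** Eight schools leave 6 degrees of freedom for a between-school comparison. A formula using normal quantiles overstates power at that size.
- **Which SD.** The paragraph calls 200 CPM the SD of change and also gives a baseline to post-test correlation. A correlation is needed only to turn a single-time SD into an SD of change (or of a baseline-adjusted outcome). If 200 CPM is already the SD of change, r = 0.30 has nothing to do.
- **The target.** The same 200 CPM is the difference to be detected over the whole school day, although the active lessons fill a small part of that day and are shorter than in the programme that supplied the figure.

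At stake is how a null result on the primary outcome is read. If the real power for the effect this amount of lesson time can produce is well below 80%, a null whole-day result could be taken as evidence of no effect when it is not.

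**Working it through.** **Inputs.** From Sample size calculation: difference 200 CPM, SD 200 CPM, r = 0.30, ICC 0.15, 25 children per school, alpha 0.05, power 80%. Two-sided testing is assumed, as sidedness is not stated. From the Abstract: 10 schools. From Intervention and Physical activity: 3 × 40 = 120 lesson-minutes a week; 5 days × 360 min = 1,800 measured minutes. From Background: 3 × 60 = 180 lesson-minutes a week in the maths trial.

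**1. Reproducing N = 200.** Design effect = 1 + (25 − 1) × 0.15 = 4.6. Total N = 4 × (1.960 + 0.842)² × (SD/200)² × 4.6.

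- 200 as a single-time SD, change scores: variance factor 2 × (1 − 0.30) = 1.4, SD 236.6. N = 202; normal-approximation power at N = 200 is 79.6%. This matches the plan.
- 200 as the SD of change: N = 144; power at N = 200 is 90.9%. This does not match.
- 200 as a single-time SD, post-test adjusted for baseline: variance factor 1 − 0.30² = 0.91, SD 190.8. N = 131; power at N = 200 is 93.3%. This does not match.

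Only the first reading returns the stated figures.

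**2. Small-cluster power at 200 CPM.** Effective n per arm = 25 × (schools/2) / 4.6, which is 21.74 for 8 schools and 27.17 for 10. Noncentrality = 200 / (SD × √(2 / effective n)). Power comes from the noncentral t distribution with degrees of freedom = schools − 2. The same ICC is assumed after baseline adjustment.

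| Reading | SD | 8 schools, 6 df | 10 schools, 8 df |
|---|---|---|---|
| Single-time SD 200, change score | 236.6 | ncp 2.79, 64% | ncp 3.12, 78% |
| SD of change 200 | 200 | ncp 3.30, 78% | ncp 3.69, 90% |
| Single-time SD 200, baseline-adjusted | 190.8 | ncp 3.46, 82% | ncp 3.86, 92% |

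**3. Matched pairs analysed as pairs.** Degrees of freedom fall to pairs − 1. With 10 schools (4 df) and no gain from matching credited, the three readings give 65%, 78% and 82%.

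**4. The whole-day target.** Lesson share = 120 / 1,800 = 6.7%.

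- If the effect arises only in lessons, a 200 CPM day average needs 200 × 1,800 / 120 = 3,000 CPM during them.
- If instead 200 CPM was a whole-day effect of the maths programme and scales with lesson time, the target becomes 200 × 120 / 180 = 133 CPM. With 10 schools and 8 df, power is then 45% (change score), 58% (SD of change 200) or 62% (baseline-adjusted).

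These two scenarios are alternatives, not steps of one argument. Both are illustrations.

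**The case against.** The strongest defence is that the sum is right: a standard cluster formula with the plan's own inputs gives N = 202 and 79.6%. That stands. The fault is one of method and definition, not arithmetic.

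Second, the trial plans 10 schools, not 8. This also stands, and it decides how serious the point is: at 200 CPM two of the three readings exceed 80% and the third misses by about two points. A reader might infer from the 64–78% for 8 schools that the planned trial lacks its promised power. The article does not support that, and those figures also leave out the 82% that 8 schools give under baseline adjustment. The two additional schools may be an allowance for loss, but the article does not say so.

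Third, the article does not commit to a change-score analysis. It specifies linear mixed models, and the change score is inferred by working back from N = 200. That is fair. It is a reason to ask which analysis the power refers to, not to claim that a poor one was chosen.

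Fourth, a reader might infer that a lesson-level effect was moved to the whole day, or that 200 CPM is out of reach. Neither can be shown. The Background's summary of the maths trial does not exclude a whole-day result in the cited sources, the article gives no CPM scale for the wrist device against which to judge 3,000 CPM, and activity outside lessons could also change. What stands is narrower: the paragraph takes no account of the shorter lessons or of their share of the day.

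**Conclusion.** The concern holds in a limited form. The 80% statement for 8 schools is too high on both change-score readings (64% or 78%) once the small number of schools is respected, and the SD behind it is ambiguous. For the 10 schools planned, power at 200 CPM is 78–92% with an unpaired t reference, so the shortfall is small or absent. It becomes material (65–82%) only if the pairs are analysed as pairs and matching brings no precision.

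The more consequential gap is the target. Nothing in the article reconciles "detect a between group difference of 200 CPM across the school day" with lessons that fill 6.7% of measured time and run 120 rather than 180 minutes a week. If the effect scales with lesson time, power with 10 schools is 45–62%.

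These results assume two-sided testing, equal clusters of 25 with complete data, an ICC of 0.15 that is unchanged by baseline adjustment, and degrees of freedom set by the number of schools.

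**What to change.** Rewrite the sample size paragraph to:

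1. give power for the 10 schools to be randomised, with small-cluster t degrees of freedom that match the analysis, including whether the pairing is retained;
2. say whether 200 CPM is a single-time SD or the SD of change, and what part r = 0.30 plays;
3. justify 200 CPM as a whole-day difference given 120 lesson-minutes a week, stating whether the source figure was a lesson or a whole-day effect, or restate the target and quote the power for it.

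In Statistical analyses, specify the primary model as post-test activity adjusted for baseline activity. At r = 0.30 this lowers the variance factor from 1.40 to 0.91.

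The cost is one rewritten paragraph, one model term and a less favourable stated power. No extra schools are needed. Reporting activity in the English lesson slot as a further outcome would help interpretation, but it is optional and not needed to correct this point.
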